## Abstract

**Background:**

Childhood anemia is highly prevalent worldwide. Improving the hemoglobin level of preschool age children could yield substantial benefits in cognitive and psychosocial development and overall health. While evidence-based recommendations for reducing childhood anemia in high anemia prevalence countries are available, there is no experimental evidence of community centered education and counseling programs, as a route to improved acceptance of iron supplements, demonstrating beneficial effects on anemia outcomes. We report on the evaluation protocol of a complex educational intervention led by the community lay health worker (LHW) and delivered to mothers of 12–59-month-old anemic children living in and visiting village day care centers in a large district of southern India.

**Methods and design:**

The study is designed as a cluster randomized controlled trial. The intervention is based on the social cognitive theory and aims to promote among mothers, anemia awareness, dietary modifications to increase iron intake in the child, and recognition of the need for enhanced adherence to supplemental iron in the anemic child. From 270 eligible villages in the study area, a sample of 60 villages will be randomized to intervention [*n* = 30] or to treatment as usual [*n* = 30] of the study. LHWs in the intervention arm will be trained to administer the following intervention components to mothers of anemic children: 1] monthly distribution of Iron and folic acid (IFA) supplements to mothers of anemic children, and 2] five monthly counseling sessions of mothers of anemic children covering: a] anemia awareness education b] IFA adherence counseling and assessment, c] dietary modification to improve iron intake, and d] hygiene and sanitation. LHWs in the control arm will distribute IFA to mothers of anemic children as in the intervention arm but will not provide monthly education and counseling support. The primary outcome is the difference between the two experimental groups in anemia cure rates of children found to be anemic at baseline. Secondary outcomes, assessed as differences between all participants in both experimental groups, are: change in mothers’ knowledge regarding anemia; 24 hour dietary iron intake; net improvement in individual hemoglobin values; serum ferritin; and the difference in overall cluster level childhood anemia prevalence. All outcomes will be measured 6 months after the start of the intervention. Multilevel linear and logistic regression models will be used to analyze differences between intervention and control groups in outcome variables.

**Discussion:**

This trial is designed to evaluate the effectiveness of an intervention intended to improve anemia cure rates in anemic children living in villages of Chamarajnagar, Karnataka a large district in south India. The extensive study of secondary endpoints will be used to identify possible weak points in the compliance to intervention delivery and uptake. This evaluation is one of the few large randomized trials evaluating the impact of an education and counseling intervention to reduce childhood anemia prevalence.

**Trial registration:**

This trial was registered with ISRCTN.com (identifier: ISRCTN68413407) on 17 September 2013.

**Electronic supplementary material:**

The online version of this article (doi:10.1186/s13063-015-1135-x) contains supplementary material, which is available to authorized users.

## Background

Over 1.6 billion people worldwide suffer from anemia and approximately 80 % of the burden of this disorder is borne by individuals living in South Asia and Africa [1–3]. Anemia is associated with a significant economic burden [4], accounts for 68.4 million years lived with disability (8.8 % of total for all conditions), increased maternal and perinatal mortality, and contributes to global mortality [5–7]. The prevalence of anemia in India is particularly high, where 50 % of reproductive age women, 59 % of pregnant women, 25 % of men, 40 % of adolescent girls, and 70 % of children under five years are anemic [8, 9]. The etiology of childhood anemia in limited resource settings is multifactorial [10–12], but in India it is mainly attributable to iron and other micronutrient deficiencies [6, 9, 13–15]. Iron deficiency anemia (IDA) is associated with cognitive and psychomotor retardation in children [16, 17], and trials of iron supplements in iron deficient children demonstrate improved outcomes [18]. The major cause of IDA in India is inadequate iron intake due to both low dietary iron content of food [19] and inadequate dietary animal protein [20]. In this context, childhood anemia appears to be mostly influenced by maternal anemia during pregnancy [8], poor nutritional and dietary iron intake [9, 19], and a combination of adverse socioeconomic factors [9].

Public health strategies addressing IDA have concentrated efforts on improving dietary iron intake by promoting population-based iron supplementation and diversification of diets, and by improving the iron content of food by fortification [21, 22]. These efforts have successfully reduced anemia prevalence in other Asian settings [20], but such benefits have not accrued in India [23, 24]. In line with WHO recommendations, the Indian government iterated the National Nutritional Anemia Control Programme (NNACP), which featured the use of iron supplements [21, 24]. More recently, launching of the national Iron + initiative by the Indian government has made anemia control more comprehensive by including an emphasis on nutrition [25]. Globally, however, challenges to childhood anemia control remain [26]. In India, inadequate procurement and distribution of iron and folic acid (IFA)[27], a perceived lack of adequate lay health worker (LHW) support in the village [27–29], and unfounded beliefs and psychological issues among individuals [9, 27] appear to hamper effective childhood anemia control. Previous research has shown that LHW-led education interventions are effective at promoting dietary modification, complementary feeding, and immunization uptake among rural communities [30–35]. We hypothesized that an educational and counseling intervention with a strong parental component specifically to reduce knowledge gaps among mothers, improve parental self-efficacy, and enhance adherence of the anemic child to (IFA would achieve better anemia cure rates than treatment as usual. This paper describes the study protocol for the Karnataka Anemia Project 2, which evaluates the effectiveness of a community LHW-led educational and counseling intervention delivered to mothers of anemic children residing in villages located in a province of southern India. We follow the CONSORT statement for reporting of cluster randomized trials [36, 37].

### Design and Methods

#### Study design and setting

The study is designed as a cluster randomized controlled trial (CRCT) set in the Chamarajnagar taluk, Chamarajnagar district of Karnataka state, India. Karnataka, a south western state with a population of 61 million (7.1 million of which are children 0–6 years of age) is the ninth most populated state in India (2011 census) [38]. The study area, Chamarajnagar district, is located in a rural setting with a predominantly agrarian economy and an average annual household income of Indian rupees (INR) 22 006 (US $478) reflecting state and national averages. The Karnataka average annual household income is INR 26 123 (US $567), and the Indian overall average annual household income is INR 25 825 (US $561). Literacy rates are slightly higher (total = 75 % M = 82 %; F = 66 %) than the national average.

In India, the Integrated Child Development Service (ICDS) runs a network of village-based child care centers (ADCs), caring for children up to age 6 years and potentially offering the setting in which to deliver health interventions to mothers of registered children [35]. The LHW in charge of the ADC is an integral component of the health system whose routine work includes the maintenance of childhood immunization records, health education for mothers, as well as kindergarten education for all village children. From the age of 36 months, children attend the ADC and receive day care services, education, and nutritional supplements under a government funded ICDS scheme. Although children younger than 36 months are registered in the ADC, for practical reasons they are not encouraged to attend. Typically the ADC LHW lives in the village, has a good relationship with mothers of children below 6 years of age, and an overall good standing in the community.

In this trial, a cluster (randomization unit) will be defined as a village in the Chamarajnagar subprovince that is randomly allocated to one of the study arms together with the ADC or (if the village has more than one ADC) the selected ADCs belonging to that village, and the corresponding LHW in charge of the ADC. Using a computerized random number generator [39], 60 villages from a total of 270 eligible villages will be randomly selected. The villages will be stratified based on the number of <6 year-old children listed in the ADC registers as resident in each village. After stratification, the selected villages will be assigned to intervention and control arms of the trial using a 1:1 ratio, in order to ensure equal representation of both strata to both arms. The observational units consist of children aged 12–59 months registered in the randomized villages and their mothers/caregivers, eligible for the study. We plan to recruit all eligible children (Fig. 1).

**Fig. 1 Fig1:**
[figure not shown]
Study schematic of the Karnataka Anemia Project 2 study to evaluate a community-based parental intervention to improve childhood anemia cure rate

### Participants

All children aged 12–59 months, residing in the village and registered in the village ADC, will be eligible to participate in the trial.

#### Inclusion criteria

For enrollment, children should be accompanied by their mother or caregiver. Mothers/caregivers of participants in the intervention arm should consent to receive LHW-led intervention and intend to reside in the village for at least 6 months after enrollment in the trial.

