### Protocol of recruitment

From the list of all children < 6 years registered in each village by the LHW in charge of the ADC, the research team will generate an eligible 12–59 month child list. Using this list, the LHW will mobilize participants and their mothers to the village ADC for study enrollment. Recruitment will occur at the village ADC and last for approximately 2 days. Additional house visits will be made on recruitment days to identify reasons for non-attendance of participants on the list (for example, those who are too sick, traveling, or migrating] and to help mobilize those who forgot to visit the ADC. Mothers/caregivers of all eligible children, who after being provided information about the trial indicate willingness to participate and an intention to live in the village for at least 6 months after enrollment, and those in the intervention arm indicating a willingness to receive LHW-led counseling will be enrolled after providing written informed consent (Fig. 1). Where recruitment is <80 % of the eligible list, an additional recruitment day will be allocated. Children who do not fulfill the inclusion criteria during recruitment sessions are not eligible for future recruitment.

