## Discussion

This is the first cluster randomized control trial (CRCT) designed to evaluate an intervention that includes both lay health workers and parents to complement India’s existing national health policy for combating anemia in children, one of the most pernicious and common nutritional health burdens among individuals in resource-limited settings [3, 6, 10, 51]. The present evaluation adopts a theory-based approach to investigate the causal chain through which the proposed intervention is expected to have its impact (Fig. 2). We employ qualitative methods to understand the perceptions and experiences of LHWs actually delivering the intervention and the context and process of the interventions delivery [52]. Results from this contextually relevant intervention will be used to establish whether it is possible to improve anemia cure rates in anemic children in India with relatively limited efforts targeted to the mothers of such children.

The CRCT design, whereby groups of individuals are randomly allocated to different interventions, has the potential to provide unbiased estimates of the impact of interventions delivered at the community level (in this case children in a village eligible to attend the village day care). A major strength of this trial is that it attempts to maximize participation at both the cluster and individual levels. For instance, LHWs in both arms of the study will be provided with training, support, and resources to achieve intervention goals, and will encourage cluster-level participation to minimize drop-out rates. Furthermore, randomization will be an inclusive process with active involvement and participation of the LHWs. During recruitment, the research team will actively support LHWs during periods of stress (wage-related agitations, unscheduled ADC closures for local holidays, and breaks during which LHWs perform other tasks such as immunization). The research team will perform door-to-door visits for eligible children who failed to attend the ADC after mobilization by the LHW to identify reasons for the mothers’ lack of attendance. Analysis of all this data will provide clarity regarding participation in this trial and could address concerns related to selection bias.

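### Willingness to be counseled is an entry condition in the intervention arm only, so enrollment follows allocation and risks a selection difference that plausibly favors the intervention on cure rate

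*Protocol article*

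**What the plan says.** The protocol article makes the village the unit of randomization. Under Study design and setting, "the selected villages will be assigned to intervention and control arms of the trial using a 1:1 ratio", and participants are then described in these terms: "The observational units consist of children aged 12–59 months registered in the randomized villages and their mothers/caregivers, eligible for the study".

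The Participants section makes every resident, registered child aged 12–59 months eligible, whatever the arm. The Inclusion criteria add a condition for one arm: "Mothers/caregivers of participants in the intervention arm should consent to receive LHW-led intervention". Protocol of recruitment carries it into enrollment: "those in the intervention arm indicating a willingness to receive LHW-led counseling will be enrolled after providing written informed consent". Neither section places a corresponding condition on control mothers.

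The lay health worker (LHW) brings families in: "Using this list, the LHW will mobilize participants and their mothers to the village ADC for study enrollment". Only intervention LHWs are trained to counsel (Lay health worker training), and the Discussion says that "randomization will be an inclusive process with active involvement and participation of the LHWs".

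There are safeguards. The research team, not the LHW, draws up the list of eligible children. House visits follow up non-attenders. "Where recruitment is <80 % of the eligible list, an additional recruitment day will be allocated". Hemoglobin is measured by an automated counter after consent. The Discussion plans to analyze participation with selection bias in mind, and Statistical analysis specifies intention to treat.

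**The concern.** A cluster trial keeps the benefit of randomization only if individuals enter the two arms by the same route. Here the intervention arm has an extra filter, and the filter is not neutral. The section on the rationale for the intervention lists mothers' willingness to change, attitudes and self-efficacy among the factors that shape diet and adherence to iron and folic acid. A mother who declines counseling is left out in an intervention village, whereas her counterpart in a control village is enrolled. If such mothers' children are cured less often, the intervention arm starts with a better prognosis, and part of any difference in cure rate would be selection and not effect.

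The filter acts at consent, before anemia status is known, so it applies to all intervention mothers. It can therefore also touch the comparison of village-level prevalence.

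**Working it through.** **Step 1: order of events.** The protocol gives no timeline for disclosure of allocation. However, a condition that applies to one arm can be checked only when the arm is known, and participants come from villages already randomized. Enrollment therefore follows allocation. That the LHW knows the arm is very probable, from involvement in randomization and arm-specific training, but it is not stated.

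**Step 2: the plan's own figures.** Inputs from the sample size section: cure 30% against 42%, two-sided alpha 0.05, power 80%, ICC 0.05, 25 anemic children per village, 10% loss.
- Two-proportion formula without continuity correction: 250 per arm, 500 in all (stated: 500).
- Design effect 1 + (25 − 1) × 0.05 = 2.2; 500 × 2.2 = 1,100 (stated: 1,100).
- 1,100 / 0.90 = 1,222 (stated: 1,220, so it reproduces to rounding).

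The sample size is not in dispute. It supplies the precision used below.

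**Step 3: size of a selection difference with no true effect.** Let q be the share of intervention mothers who decline counseling and r the cure rate of their children. The protocol gives neither, so both are assumptions. With 30% cure overall:

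cure among enrolled intervention children = (0.30 − q × r) / (1 − q)

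- q = 5%, r = 20%: (0.30 − 0.010) / 0.95 = 30.5%
- q = 10%, r = 15%: (0.30 − 0.015) / 0.90 = 31.7%
- q = 20%, r = 15%: (0.30 − 0.030) / 0.80 = 33.75%
- q = 20%, r = 10%: (0.30 − 0.020) / 0.80 = 35.0%
- any q, r = 30%: 30.0%

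**Step 4: false-positive rate.** With spurious difference b, null standard error s0 = √[2p̄(1 − p̄)/n] and s1 = √[(p1(1 − p1) + p2(1 − p2))/n], the chance of rejection is Φ((b − 1.96·s0)/s1) + Φ((−b − 1.96·s0)/s1). Two effective sizes per arm are used:
- The plan's 550 analyzed: 550 / 2.2 = 250.
- All 30 villages kept, with 10% loss: 30 × 22.5 / (1 + 21.5 × 0.05) = 325.

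Example, b = 0.0375 and n = 250: s0 = 0.0417, s1 = 0.0416, giving Φ(−1.06) + Φ(−2.87) ≈ 0.15.

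| Refusal q | Refuser cure r | Spurious difference | Share of 12 points | Type I error, n = 250 | Type I error, n = 325 |
|---|---|---|---|---|---|
| 5% | 20% | +0.5 | 4% | 0.052 | 0.052 |
| 10% | 20% | +1.1 | 9% | 0.058 | 0.061 |
| 10% | 15% | +1.7 | 14% | 0.069 | 0.075 |
| 20% | 15% | +3.75 | 31% | 0.15 | 0.18 |
| 20% | 10% | +5.0 | 42% | 0.22 | 0.27 |
| any | 30% | 0 | 0% | 0.05 | 0.05 |

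The 20% ceiling is the largest recruitment shortfall that triggers no extra day. That margin also absorbs illness, travel and migration, which arise in both arms, so it is a high figure for refusal of counseling alone.

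**The case against.** The strongest reply is that the documents show neither the direction nor the size. This stands in part.

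- **Direction.** A reader might infer a bias toward the intervention on every outcome. The documents do not support that. Changes in knowledge, hemoglobin and ferritin are measured from baseline; excluding less motivated mothers could raise baseline values and leave less room to improve. Nor does mobilization by an LHW who knows the arm have a documented direction: an intervention LHW might bring in harder-to-reach mothers.
- **Size.** Mothers who accept a trial with venous sampling may seldom refuse counseling. Mild assumptions give about half a point, and the difference is zero if refusers do not differ.
- **Selection on anemia.** A reader might suspect LHWs of choosing which anemic children enter. They cannot, because hemoglobin is measured after enrollment and the research team generates the list.
- **Residence.** The Inclusion criteria can be read as asking for the 6-month residence intention in one arm only. Protocol of recruitment applies it to all, so this is a wording conflict and not a second unequal criterion.

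The safeguards limit or describe the problem without removing it. House visits and the extra day address attendance, not the entry condition. Participation counts cannot supply outcomes for children never enrolled, and intention to treat covers enrolled children only. The planned covariates (age, sex, socioeconomic status, literacy, nutrition, maternal anemia) do not include maternal motivation.

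**Conclusion.** The concern holds as a defect in the entry rule. Willingness to be counseled is required in one arm only, in conflict with the protocol's own statement of who is eligible, and after the arm is known. It risks a selection difference that plausibly favors the intervention on the primary cure rate. That direction rests on the protocol's own causal reasoning, not on data, and should not be extended to the change-from-baseline outcomes.

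Under the assumptions above the spurious difference runs from 0 to about +5 points. The case of 10% refusal and 15% cure gives +1.7 points and a type I error of about 7%; 20% and 15% gives +3.75 points and about 15–18%. These are illustrations, not estimates. The case for changing the rule does not depend on them: with the rule in place, the trial could not show afterwards that the selection difference was zero.

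**What to change.** 1. **One entry rule.** Drop willingness to be counseled as an entry criterion. Seek consent to measurement and follow-up in the same terms in both arms, and treat acceptance of counseling as a separate question. Keep intervention mothers who decline counseling enrolled, followed and analyzed in their randomized arm. Align the residence wording in the Inclusion criteria with Protocol of recruitment.
2. **Villages recruited under the current rule.** Report by arm the numbers eligible, approached, enrolled and refusing counseling, and add a sensitivity analysis by enrollment rule.
3. **Villages whose allocation has not yet been disclosed, if there are any.** Complete listing, consent and baseline measurement before disclosure. Where LHWs already know the arm, as the Discussion suggests, this step is not available.

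Cost: an amendment to the eligibility and consent wording. Recruitment is stated to run from November 2014 to July 2015, so a change made after it has begun leaves two enrollment rules within one trial. Including decliners may also reduce the estimated effect. The sample size calculation itself does not change.

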#### Exclusion criteria

Children with severe anemia defined as Hb ≤ 7.9 gm/dl for the purpose of this trial [40] will be excluded and referred to the primary health center/first referral unit for assessment and medical management. Children with a reported history of an active infection or fever >101 °F will also be excluded from participation and referred to the primary health center/first referral unit for management as usual.

### Intervention

#### Rationale for the intervention and its development

In the planning stage of the intervention, theoretical frameworks were developed according to Fraser et al [41]. In the Problem Theory, the mother’s knowledge, attitude, beliefs, care and control, role model, willingness to change, and parental self-efficacy were identified as malleable factors in order to influence the hygiene, dietary habits, and adherence to IFA supplements in their children. The design of the intervention is guided by the Social Cognitive Theory (SCT) [42], based on evidence in the published literature [23, 29, 31, 33, 34, 43, 44], and modulated based on discussions with stakeholders and policymakers in the Karnataka. According to the SCT, at least two principal sources of self-efficacy: verbal persuasion and performance accomplishment, are intended to mediate the effect of this intervention. The education of mothers about anemia, nutrition, IFA supplementation, and hygiene could foster the perception that their actions can control anemia in their children. This would lead to positive expectations about their children’s health outcomes, which, along with LHW facilitation of learning and positive reinforcement, could improve IFA adherence (Fig. 2).

